## Abstract

**Background:**

The microbiota is increasingly recognized as a significant factor in the pathophysiology of many diseases, including cardiometabolic diseases, with lifestyles probably exerting the greatest influence on the composition of the human microbiome. The main objectives of the study are to analyze the association of lifestyles (diet, physical activity, tobacco, and alcohol) with the gut and oral microbiota, arterial aging, and cognitive function in subjects without cardiovascular disease in the Iberian Peninsula. In addition, the study will examine the mediating role of the microbiome in mediating the association between lifestyles and arterial aging as well as cognitive function.

**Methods and analysis:**

MIVAS III is a multicenter cross-sectional study that will take place in the Iberian Peninsula. One thousand subjects aged between 45 and 74 years without cardiovascular disease will be selected. The main variables are demographic information, anthropometric measurements, and habits (tobacco and alcohol). Dietary patterns will be assessed using a frequency consumption questionnaire (FFQ) and the Mediterranean diet adherence questionnaire. Physical activity levels will be evaluated using the International Physical Activity Questionnaire (IPAQ), Marshall Questionnaire, and an Accelerometer (Actigraph). Body composition will be measured using the Inbody 230 impedance meter. Arterial aging will be assessed through various means, including measuring medium intimate carotid thickness using the Sonosite Micromax, conducting analysis with pulse wave velocity (PWA), and measuring pulse wave velocity (cf-PWV) using the Sphygmocor System. Additional cardiovascular indicators such as Cardio Ankle Vascular Index (CAVI), ba-PWV, and ankle-brachial index (Vasera VS-2000^®^) will also be examined. The study will analyze the intestinal microbiota using the OMNIgene GUT kit (OMR−200) and profile the microbiome through massive sequencing of the 16S rRNA gene. Linear discriminant analysis (LDA), effect size (LEfSe), and compositional analysis, such as ANCOM-BC, will be used to identify differentially abundant taxa between groups. After rarefying the samples, further analyses will be conducted using MicrobiomeAnalyst and R v.4.2.1 software. These analyses will include various aspects, such as assessing α and β diversity, conducting abundance profiling, and performing clustering analysis.

**Discussion:**

Lifestyle acts as a modifier of microbiota composition. However, there are no conclusive results demonstrating the mediating effect of the microbiota in the relationship between lifestyles and cardiovascular diseases. Understanding this relationship may facilitate the implementation of strategies for improving population health by modifying the gut and oral microbiota.

**Trial registration:**

clinicaltrials.gov/ct2/show/NCT04924907, ClinicalTrials.gov, identifier: NCT04924907. Registered on 21 April 2021.

## 1. Introduction

The gut microbiota consists of a diverse community of 10^13^ to 10^14^ bacteria, archaea, and eukaryotes, with the number of genes represented being more than two orders of magnitude greater than the human genome (1). Although relatively stable in adults, the gut microbiome can be altered by diet and medications (2). Most of the microbial populations belong to the domain of bacteria, with ~90% belonging to the phyla *Bacteroidetes* and *Firmicutes* (3). Metabolites produced by gut bacteria include short-chain fatty acids, which can provide ~10% of the daily energy requirement in humans, regulate glucose homeostasis and cholesterol metabolism, and modulate the immune system (4). Bile acids, which are involved in the absorption of fat-soluble vitamins, regulate triglycerides and contribute to the maintenance of intestinal barrier function, in addition to exerting antimicrobial effects depending on their type and concentration (5). Lipopolysaccharides are associated with insulin resistance and impaired intestinal homeostasis, leading to increased permeability of the intestinal membrane that allows bacteria to translocate, activating the immune system and inducing inflammation (6). The oral cavity is the gateway to the digestive and respiratory systems and is highly vascularized, indicating the possible involvement of the oral microbiome in some systemic diseases such as cardiovascular, endocrine, cancer, and other diseases; the most prevalent phyla are *Firmicutes, Proteobacteria, Actinobacteria, Bacteroides, Fusobacteria*, and *Spirochetes* (7).

Although intestinal architecture, genetically defined traits, and age are the factors most strongly influencing the composition of the intestinal microbiome (8), diet and lifestyle are likely the major causes of interindividual variation in its composition in humans. A multitude of factors, such as restrictive diets and strict vegan or gluten-free diets, have been shown to change the intestinal microbiota and can contribute to intestinal dysbiosis (3). Obesity is related to reduced fecal microbial diversity, just as a high-salt diet leads to dysbiosis (3). Physical exercise also has a positive impact on the biodiversity of the microbiota, as some studies on animals and humans have shown (4, 9). Nevertheless, while evidence suggests that the microbiota plays a key role in maintaining systemic nitric oxide (NO) homeostasis, causal inferences regarding healthy aging are limited (10). There are also no conclusive studies analyzing the relationship between oral microbiomes and different lifestyles.

The gut microbiome changes across the lifespan, reaching maturity at 2–3 years, remaining relatively stable during adulthood, and beginning to change as the host starts to age (11). During the aging process, the gut microbiome becomes unstable and experiences a decrease in diversity (12). The loss of bacterial diversity in the intestine of older adults has been associated with increased frailty and reduced cognitive performance, as well as the institutionalization of aging individuals and reduced physical activity (13). Dysbiosis has been associated with several diseases and conditions prevalent in older adults, including type 2 diabetes, frailty, insulin resistance, atherosclerosis, hypertension, Alzheimer's disease, and others (4). Some associations have also been found with parameters of arterial aging, such as an increase in intima-media thickness (IMT) with the abundance of *Serratia* and *Blautia* and a greater presence of *Bacteriodes* associated with a higher pulse wave velocity in subjects without diabetes (14). In a cohort of women in the UK, an inverse association between the diversity of the intestinal microbiota and arterial stiffness was found (15). Although there are no specific studies on the oral microbiome and vascular aging, evidence would suggest that oral bacteria play an important role in mediating the beneficial effects of nitrate-rich foods on blood pressure (16) and, thus, vascular function.

Dysbiosis is characterized by the presence of more proinflammatory species that favor the development of metabolic diseases, either by independent or diet-dependent mechanisms. It can affect the metabolic state of the organism in addition to significantly impacting blood pressure, glycemia, and atherosclerosis, which are all cardiovascular risk factors (17). Such dysbiosis can increase intestinal permeability and favor the subsequent displacement of molecules produced by the intestinal microbiota, for example, phosphatidylcholine, choline, betaine, and L-carnitine, which are abundant in red meat and dairy products and are converted into trimethylamine, which is associated with the development and progression of cardiovascular disease (18). The composition of the intestinal microbiota is also linked to the early stages of hypertension (19), obesity, insulin resistance, metabolic syndrome, and type 2 diabetes (4). A meta-analysis (20) has confirmed the presence of 23 oral commensal bacteria, either individually or in coexistence, within atherosclerotic plaques in patients undergoing carotid endarterectomy, catheter atherectomy, or similar procedures. Nevertheless, the precise relationship between oral microbiota and atherosclerotic disease is yet to be fully clarified.

A mounting body of evidence suggests that altered gut microbiome composition is involved in the development of adipose tissue dysfunction and insulin resistance (21). In recent years, the intestinal microbiota has also been found to be involved in responses to type 2 diabetes mellitus treatment (22), with drug-induced metabolites transforming the structure of the gut microbiota (23). A recent epidemiological study indicated an association between mouthwash use and an elevated risk of developing prediabetes and diabetes, presumably by killing nitrate-reducing bacteria that can affect nitric oxide availability (24).

Microbial dysbiosis can lead to atherosclerosis, cerebrovascular disease, and endothelial dysfunction, which are risk factors for vascular cognitive impairment (18). In patients with Alzheimer's disease, the number of *Firmicutes* and *Actinobacteria* has been shown to decrease while those of *Bacteroidetes* increase, with a parallel decrease in *Eubacterium* and an increase in *Escherichia/Shigella*, defined as proinflammatory (25). However, the etiology of this fact remains unclear. Some longitudinal studies suggest a causal relationship between chronic periodontitis and the development of Alzheimer's disease (26). However, although a possible mediation of this relationship by the presence of oral gingipains in the brain has been posited, the explanation of how periodontitis or oral microbiome dysbiosis can lead to dementia remains unclear (26).

The study on position by the ESC Working Group on Coronary Pathophysiology and Microcirculation (27) points out that studies on the microbiome are hindered by the complexity of the measurements, as well as heterogeneity in terms of study design, methods used, sampling, parameters measured, and populations studied; furthermore, they are not sufficiently powerful as a rule to capture substantial variation in the gut microbiome. Moreover, to date, there is no universally accepted consensus as to what constitutes a healthy microbiome, and inter-individual variability is enormous. Thus, there remain many knowledge gaps regarding the factors influencing intestinal microbiota with a view to achieving a healthier profile. There is some evidence regarding the modification of lifestyles, but these results need to be confirmed by studies with greater power and population diversity. Meanwhile, although some studies hint at the relationship of the microbiota with arterial aging, the profile of a healthy cardiovascular and neurocognitive microbiota remains to be clearly established. Finally, little is known about the mediating role of the microbiota in the relationship of lifestyles with health, cardiology, and cerebrovascular disease.

For all these reasons, the objectives of this MIVAS III study are to analyze the relationship between lifestyles (eating patterns, regular physical activity, smoking, and drinking) and the gut and oral microbiota, along with anthropometric parameters and aging arterial, cardiovascular, and neurocognitive health in the general Spanish population. Similarly, the mediating role of the gut and oral microbiota in the relationship between lifestyles and vascular health will be analyzed. Gender differences in the association of lifestyles with the composition of the gut and oral microbiota and vascular structure and function will also be analyzed. In addition, the study will examine the opinions and experiences of the population through a discussion group to facilitate the transfer from the study to routine clinical practice.

## 2. Methods and analysis

### 2.1. Study design and setting

In its first phase, this study is designed as a multicenter cross-sectional study that aims to analyze associations between lifestyles and gut microbiota components, as well as the relationship between the gut microbiota and arterial aging. The second phase involves cohort follow-up. Here, discussion groups will bring out the opinions and experiences of the population regarding the influence of microbiota composition on health. The MIVAS III study (PI20/00321) was registered with ClinicalTrials.gov (registration number: NCT04924907) on 21 April 2021. This project is to be conducted within 3 years of Clinicaltrials.gov registration. The first 2 years will be spent conducting sample selection and data gathering through the questionnaires and explorations described below. In the third year, the analysis and dissemination of the results will be carried out. The study was approved by the “Committee of Ethics of Research with Medicines of the Health Area of Salamanca” on 13 November 2020 (cod. 2020 10 568). A SPIRIT (Standard Protocol Items: Recommendations for Interventional Trials) checklist (28) is available for this protocol (Supplementary material 1).

The study will be carried out in primary healthcare facilities within the scope of the Network for Research on Chronicity, Primary Care, Prevention, and Health Promotion (RICAPPS) in Spanish centers (Salamanca, Valladolid, Zaragoza, and Palma de Mallorca) and the Iberian network on arterial structure, central hemodynamics, and neurocognition, with the participation of Spanish and Portuguese researchers. Microbiota analysis will be carried out at the Cancer Research Center of Salamanca and in the Department of Health and Genomics of the University of Valencia.

### 2.2. Study population

One thousand participants will be selected from users of Spanish primary healthcare centers who meet the following inclusion criteria: being aged between 45 and 74 years and not meeting any of the exclusion criteria, which include the following: cardiovascular disease; body mass index (BMI) > 40 kg/m^2^; severe renal failure; chronic inflammatory or bowel disease; oncology disease under treatment; terminal state; pregnancy; and use of antibiotics in the previous 2 weeks. Participants will be recruited at health centers with the active participation of family doctors and nurses.

The sample size for this study was calculated with the free software GRANMO (http://www.imim.cat/ofertadeserveis/software-public/granmo/). The size necessary to detect the difference of 0.1 points in the alpha diversity of the microbiota (Shannon index) between the subjects that do or do not meet the Mediterranean diet criteria has been estimated. The proportion of compliance with the Mediterranean diet in the Evident II study was 30% (29). Therefore, assuming an alpha risk of 0.05 and a beta risk of 0.2 in a two-sided test, a common standard deviation of 0.4 (30), and a 5% dropout rate due to technical difficulties or refusal to participate, 190 subjects in the first group and 436 in the second are required to detect a difference ≥0.1 point between them in the Shannon index. On the other hand, assuming a rate of exposure of 0.3% (dysbiosis), in the control group, 471 subjects with vascular aging and 471 controls are required to detect a minimum odds ratio of 1.5 in the study factor (alpha diversity). Therefore, the 1,000 participants to be included in the study will be enough to test the mentioned hypotheses and will have an equal gender distribution.

While patients did not participate in the design of the study, they will actively participate in recruitment by disseminating the study objectives and inclusion criteria through their organizations. At the end of the study, in addition to sending a detailed report with the results of each patient, a dissemination session will be organized for all patients included in the study. Through discussion groups, the opinions and experiences of the population regarding the influence of microbiota composition on health will be investigated. Similarly, their attitudes and possible resistance will be considered for the transfer to clinical practice.

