The MIVAS I (80) was a case-control study conducted in Spain (Salamanca) and Portugal (Guimaraes), with subjects from the EVA study (81) and the Cunha et al. (82), respectively, with the aim of analyzing the influences of gut microbiota on arterial stiffness. In this study, subjects with arterial stiffness and controls with the same characteristics were selected from the aforementioned studies. The MIVAS III study will select the general population of patients attended by family doctors and nurses in primary healthcare centers in different Spanish cities (Salamanca, Valladolid, Zaragoza, and Palma de Mallorca). The design is a multicenter cross-sectional study, with the main objective of analyzing the relationship between lifestyles (eating patterns, regular physical activity, smoking, and drinking) and the oral and gut microbiota. Second, the mediating role that the oral and gut microbiota may have in the relationship between lifestyle and arterial aging. In addition, the study will examine the opinions and experiences of the population through a discussion group to facilitate the transfer from the study to routine clinical practice. Finally, the second phase of the MIVAS III study will follow up on the cohort to analyze the effect of different oral and gut microbiota patterns on population health.

In conclusion, as previously discussed, healthy lifestyles, such as adequate dietary intake, a moderate or high level of physical activity, and not smoking, are beneficial for improving health and reducing the risk of many diseases, including cardiovascular diseases. It has also been found that lifestyles, particularly diet but also physical activity, act as modifiers of the composition and function of the microbiota. Nevertheless, no conclusive results have demonstrated the mediating effect of the microbiota in the relationship between lifestyles and cardiovascular diseases. Knowledge of the influence of different lifestyles on the composition of the gut and oral microbiome and of this on arterial aging and cardio- and cerebrovascular target organ lesions may facilitate the implementation of strategies to improve the health of the population by modifying the gut and oral microbiota.

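### The sample-size section justifies 1,000 participants for vascular aging with a balanced 471-versus-471 comparison, but an unselected cross-sectional sample fixes no such split, so sufficiency depends on a prevalence that is not stated

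*Protocol article*

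**What the plan says.** Section 2.2 of the protocol article (Study population) contains two calculations.

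- **Diet and Shannon index.** This takes 30% compliance with the Mediterranean diet and arrives at 190 and 436 subjects, a split close to 30:70. It works under "assuming an alpha risk of 0.05 and a beta risk of 0.2 in a two-sided test" and allows for "a 5% dropout rate due to technical difficulties or refusal to participate".
- **Vascular aging.** This is introduced by "assuming a rate of exposure of 0.3% (dysbiosis), in the control group" and continues: "471 subjects with vascular aging and 471 controls are required to detect a minimum odds ratio of 1.5".

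The paragraph then draws one conclusion for both: "Therefore, the 1,000 participants to be included in the study will be enough to test the mentioned hypotheses". The only distribution it fixes for the 1,000 is an equal split by sex.

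Section 2.1 calls the first phase a multicenter cross-sectional study. Section 3 repeats this: "The design is a multicenter cross-sectional study, with the main objective of analyzing the relationship between lifestyles". Section 3 also describes the earlier MIVAS I study as the case-control study that selected people with arterial stiffness and comparable controls. It contrasts that with MIVAS III, which takes the general population attending primary care.

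**The concern.** A requirement of 471 per group suits a design in which the investigator chooses how many affected and unaffected people to enrol. Here nobody chooses. Participants are primary-care users aged 45 to 74 without cardiovascular disease, and no section selects, enriches, matches or sets a quota on vascular aging. The number affected will be whatever the prevalence produces. The only visible link between the calculation and the conclusion is that 471 + 471 = 942 is below 1,000.

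The same paragraph does this properly for diet, where the expected 30:70 split enters the calculation. The vascular-aging calculation drops that step.

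The relationship between gut microbiota and arterial aging is a stated aim in section 2.1, and this is the article's only power statement for it. If the prevalence is well away from one half, readers are told that the sample is enough when power for an odds ratio of 1.5 may be clearly below 80%. A null result on the binary outcome could then be read as stronger evidence against such an association than it is.

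**Working it through.** **Inputs**

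- Two-sided alpha 0.05 and power 0.80: stated in section 2.2 for the diet calculation; assumed to carry over.
- Dropout 5%: likewise stated for the diet calculation and assumed to carry over.
- Exposure in controls: printed as 0.3%; taken as p0 = 0.30 (justified in step 1).
- Odds ratio 1.5, 1:1 groups, total 1,000: section 2.2.
- Prevalence of vascular aging: not given; varied from 10% to 50% and beyond as an assumption.

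**Step 1: reproduce 471**

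Exposure among the affected: p1 = 1.5 × 0.30 / (0.70 + 1.5 × 0.30) = 0.45 / 1.15 = 0.3913. The mean of the two proportions is 0.3457.

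Two-proportion formula with pooled null variance, per group:

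n = [1.96 √(2 × 0.3457 × 0.6543) + 0.842 √(0.3913 × 0.6087 + 0.30 × 0.70)]² / 0.0913² = 425 (rounded up).

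The continuity correction raises this to 447, and 447 / 0.95 = 470.5, which rounds up to 471. That is an exact match, so 471 is a pure 1:1 figure.

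Taking 0.3% literally (0.003), the same method gives 27,600 per group, or 29,053 after dropout. No variant tried with 0.003 comes near 471.

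**Step 2: what 471 in each group would require**

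To find both groups among 1,000 unselected people, prevalence must be at least 47.1% (471 / 1,000) and at most 52.9% (529 / 1,000). This is stricter than needed, because unequal groups can still give 80% power.

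**Step 3: let the split follow the prevalence**

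With 1,000 × 0.95 = 950 evaluable, set n1 = 950 × prevalence and n0 = 950 − n1, and keep p0, p1 and alpha. Then:

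power = Φ{[(p1 − p0) − 1.96 × SE0] / SE1}

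Here SE0 is the pooled and SE1 the unpooled standard error. Example at 20%: n1 = 190, n0 = 760, pooled proportion 0.3183, SE0 = 0.0378, SE1 = 0.0391. So (0.0913 − 1.96 × 0.0378) / 0.0391 = 0.44, and Φ(0.44) = 0.67.

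| Prevalence (assumed) | Power, uncorrected | Power, continuity-corrected | Minimum OR at 80% power, uncorrected | Total to recruit for OR 1.5 (corrected, 5% dropout) |
|---|---|---|---|---|
| 10% | 45% | 41% | 1.86 | 2,558 |
| 15% | 58% | 54% | 1.69 | 1,811 |
| 20% | 67% | 64% | 1.60 | 1,448 |
| 30% | 78% | 76% | 1.52 | 1,110 |
| 40% | 83% | 81% | 1.48 | 977 |
| 50% | 84% | 83% | 1.47 | 942 |

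Power is at least 80% for prevalences of about 37% to 62% with the continuity correction, the method that reproduces 471. Without it, the range is about 33% to 65%.

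**Step 4: what is not affected**

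- Diet and Shannon index: a difference of 0.1, SD 0.4 and a 30:70 split give 180 and 420, or 190 and 443 after dropout, close to the printed 190 and 436. With 950 evaluable, power is about 0.94.
- A continuous arterial measure against continuous Shannon: the correlation detectable with 80% power is tanh(2.80 / √(950 − 3)) = tanh(0.091) ≈ 0.09, whatever the prevalence.

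**The case against.** The strongest counter-argument is that no shortfall is shown. A reader might infer that 1,000 suffices only if prevalence is very close to one half. The documents do not support that: it is true of the literal 471/471 requirement, but with unequal groups 1,000 is enough over a broad band. A reader might also infer that the study is underpowered. That is not supported either. The article gives no prevalence and no single binary definition of vascular aging. Sections 2.3.4.1 to 2.3.4.4 list several measures, and the CAVI classification alone has cut-offs at 8 and 9. Depending on the definition, the affected share could lie inside or outside the adequate range. A condensed article may also leave that definition to the full protocol.

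Three further points carry weight. Section 3 puts lifestyles and microbiota first and mediation towards arterial aging second. Section 2.4 already plans analyses that need no dichotomy, including correlations and linear regression for mediation. And the 80% power and 5% dropout are not stated for the odds-ratio calculation; they are inferred.

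These points limit the size and reach of the concern. They do not restore the conclusion drawn in section 2.2, which rests on a split that the design does not provide. The exact match at 471 makes the carried-over inputs a reasonable reading.

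**Conclusion.** The concern holds in a conditional form. The statement that 1,000 participants suffice for the vascular-aging hypothesis does not follow from the 471/471 calculation, because recruitment does not fix the split and no prevalence is stated. The claim is right if prevalence is about 37–62% (33–65% uncorrected) and wrong outside that range. The gap is small at 30% prevalence and serious at 10–20%.

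This rests on reading the printed 0.3% as 0.30, on carrying over alpha, power and dropout from the diet calculation, and on an assumed prevalence. It concerns the binary vascular-aging comparison only.

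**What to change.** Keep N at 1,000 and revise the sample-size paragraph in section 2.2:

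1. Correct the exposure rate from 0.3% to 0.3 (30%), and state the alpha, power and dropout used for this calculation.
2. Remove the 471/471 sufficiency statement and do one of the following:
   - name the binary definition of vascular aging used, and report power and minimum detectable odds ratio over a stated prevalence range, for example 10–50%; or
   - base the hypothesis on a continuous arterial measure already collected, such as cf-PWV, against continuous Shannon, and state that 950 evaluable participants detect a correlation of about 0.09 with 80% power.

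The cost is rewording one paragraph; recruitment and measurements do not change. The drawback is that the stated power for the binary outcome becomes less favourable.
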